# Pulsed radiofrequency or anterior neurectomy for anterior cutaneous nerve entrapment syndrome (ACNES) (the PULSE trial): study protocol of a randomized controlled trial

**DOI:** 10.1186/s13063-017-2110-5

**Published:** 2017-08-02

**Keywords:** Abdominal pain, Randomized controlled trial, Chronic pain, Pain management, Surgical procedures, Operative, Pulsed radiofrequency treatment

## Abstract

**Background:**

Some patients with chronic abdominal pain suffer from an anterior cutaneous nerve entrapment syndrome (ACNES). This somewhat illusive syndrome is thought to be caused by the entrapment of end branches of the intercostal nerves residing in the abdominal wall. If ACNES is suspected, a local injection of an anesthetic agent may offer relief. If pain is recurrent following multiple-injection therapy, an anterior neurectomy entailing removal of the entrapped nerve endings may be considered. After 1 year, a 70% success rate has been reported. Research on minimally invasive alternative treatments is scarce. Pulsed radiofrequency (PRF) treatment is a relatively new treatment for chronic pain syndromes. An electromagnetic field is applied around the nerve in the hope of leading to pain relief. This randomized controlled trial compares the effect of PRF treatment and neurectomy in patients with ACNES.

**Methods:**

Adult ACNES patients having short-lived success following injections are randomized to PRF or neurectomy. At the 8-week follow-up visit, unsuccessful PRF patients are allowed to cross over to a neurectomy. Primary outcome is pain relief after either therapy. Secondary outcomes include patient satisfaction, quality of life, use of analgesics and unanticipated adverse events. The study is terminated 6 months after receiving the final procedure.

**Discussion:**

Since academic literature on minimally invasive techniques is lacking, well-designed trials are needed to optimize results of treatment for ACNES. This is the first large, randomized controlled, proof-of-concept trial comparing two therapy techniques in ACNES patients. The first patient was included in October 2015. The expected trial deadline is December 2017. If effective, PRF may be incorporated into the ACNES treatment algorithm, thus minimizing the number of patients requiring surgery.

**Trial registration:**

Nederlands Trial Register (Dutch Trial Register), NTR5131 (http://www.trialregister.nl/trialreg/admin/rctview.asp?TC=5131). Registered on 15 April 2015.

**Electronic supplementary material:**

The online version of this article (doi:10.1186/s13063-017-2110-5) contains supplementary material, which is available to authorized users.

## Background

Chronic abdominal pain originating in the abdominal wall is termed chronic abdominal wall pain (CAWP). A CAWP syndrome may be caused by the anterior cutaneous nerve entrapment syndrome (ACNES). At present, ACNES is still often neglected as a possible cause of abdominal pain and discomfort and a frequently overlooked diagnosis [1, 2]. An exact pathophysiological explanation of the syndrome is currently lacking but may be related to alterations in abdominal wall neuroanatomy.

The abdominal wall is sensory innervated by anterior and lateral cutaneous branches of the anterior rami of the thoracic intercostal nerves (7th to 12th) [3]. In ACNES, normal function of one or more cutaneous branches of the thoracic intercostal nerves is disturbed by a hitherto unidentified event [3]. If ACNES is suspected, current treatment options include analgesics, subfascial injections of a local anesthetic (whether or not combined with a long-acting corticosteroid), transcutaneous electrical nerve stimulation (TENS) and surgical interventions such as anterior and posterior neurectomy. Injection therapy is effective in one third of patients in the long term [4]. A neurectomy is usually considered in the remaining two thirds with a reported 70% success rate [5].

Although neurectomy is effective in most patients, a less-invasive procedure may be of potential benefit. Pulsed radiofrequency (PRF) is a relatively minimally invasive treatment that was initially designed as a less destructive approach when compared to radiofrequency (RF) therapy. Using the intermittent administration of high-frequency currents, tissue temperatures do not exceed 42 °C, thus preventing neuronal damage [6, 7]. A number of clinical studies have shown potential as levels of chronic pain in a variety of pain syndromes were significantly reduced [8, 9]. Evidence regarding the use of PRF in ACNES is limited to two case reports on PRF treatment of the dorsal root ganglion (DRG) resulting in pain reduction and improved quality of life [10, 11].

The objective of the present paper is to discuss a randomized trial comparing PRF with neurectomy as treatment options in ACNES. Neurectomy is nowadays considered the “gold standard” treatment but less invasive methods may potentially be of benefit.

## Methods

### Trial design

This prospective, multicentre, non-blinded, proof-of-concept, randomized controlled trial (with a one-way optional crossover at 8 weeks) is performed in the SolviMáx Center of Expertise for ACNES and Center of Excellence for Abdominal Wall and Groin Pain and Maasziekenhuis Pantein, Boxmeer, The Netherlands. SolviMáx is a subdivision of the Surgical Department of Máxima Medical Center (MMC), a teaching hospital situated in the southern part of The Netherlands. The Dutch Ministry of Health, Welfare and Sport has certified SolviMáx as a Center of Expertise for ACNES treatment. The trial will be based on a clinical proof-of-concept design in order to investigate a potential difference in pain relief following either PRF treatment or an anterior neurectomy in ACNES. Furthermore, it is designed to attain more knowledge on the use of PRF on peripheral nerves and to detect possible side effects.

The present trial follows the guidelines of the Declaration of Helsinki (version 19 October, 2013). The protocol (protocol number NL53171.015.15) is approved by the Medical Ethics Committee of MMC. The study protocol (version 1) is registered at www.trialregister.nl (NTR registration number: 5131, date of registration 15 April 2015). The present paper is written according to the Standard Protocol Items: Recommendations for Interventional Trials (SPIRIT) 2013 Statement for reporting a clinical trial protocol [12]. The SPIRIT Checklist is provided as Additional file 1.

### Participants

Patient enrollment started in October 2015. Patients are identified at the two hospital facilities. Criteria for the diagnosis ACNES are (1) a constant site of tenderness that is superficially located covering a fingertip-sized point of maximal pain at the lateral border of the rectus abdominis muscle, (2) a somewhat larger area of altered skin sensation covering this tender point and (3) observing that tenderness increases by abdominal muscle tensing using Carnett’s test [13, 14]. Only adult patients (over 18 years old) diagnosed with unilateral ACNES and having temporary success from an injection regimen will be invited for participation. In ACNES, a treatment regimen consists of local abdominal wall infiltration using 5–10 mL lidocaine as described in our earlier studies [4, 15]. “Temporary” is defined as having more than 50% pain reduction for at least 1 week after such a local infiltration although symptoms recur afterwards (refractory ACNES). Sixty-six patients (male or female) will be enrolled in the trial. Patients are not eligible if pain is caused by surgical scar-related pain syndromes (i.e., point of maximum pain is located at the site of a surgical scar) or due to recent intra-abdominal pathology. Presence of other chronic pain syndromes including fibromyalgia, dystrophy, chronic low back pain, impaired communication, a previous spinal surgical procedure at or between vertebral levels T7 and L1 are also exclusion criteria. A full list of inclusion and exclusion criteria is given in Table 1. Once eligibility is determined, patients are counseled on the specifics of the study and are given a number of days prior to providing consent.

**Table 1 Tab1:** Subject inclusion and exclusion criteria

Inclusion criteria	Exclusion criteria
• Patient is diagnosed with unilateral anterior cutaneous nerve entrapment syndrome (ACNES)	• Patient has surgical scar-related pain syndromes
• Eligible for neurectomy (i.e., having temporarily success using injection therapy)	• Patient has recent intra-abdominal pathology
• Patient >18 years old	• Patient has other chronic pain syndromes (such as fibromyalgia, dystrophy, chronic low back pain)
• Patient is able to provide written informed consent	• Patient has other neuropathic diseases
• Patient is willing to participate in the follow-up schedule and protocol	• Patient has impaired communication
	• Patient has participated in another clinical investigation within 30 days
	• Patient has had a spinal surgical procedure at or between vertebral levels T7 and L1
	• Patient has been diagnosed with cancer in the past 2 years, except for skin malignancies
	• Female patient of childbearing potential is pregnant/nursing or plans to become pregnant during the course of the trial
	• Significant anatomic deformity (either congenital or acquired)
	• Language barrier
	• Allergy to local anesthetics

### Interventions

#### PRF arm

Patients will be randomized to one arm of treatment, either PRF or an anterior neurectomy. Patients assigned to the PRF arm will visit departments of pain management of both hospitals for PRF treatment. While supine, a maximal point of pain is determined by asking and by a physical examination. In ACNES, there is characteristically a small (<2-cm^2^) constant site of anterior abdominal tenderness. Following marking, the skin is prepped with betadine and draped. Ultrasound (US) is used to locate the anterior fascia of the rectus abdominis muscle. The skin is locally anesthetized using 1% lidocaine. A straight, sharp RF cannula (SMK Pole needle 54 mm with 5-mm active tip, Cotop International BV, Amsterdam, The Netherlands) is inserted at an approximately 45° angle through the skin (Fig. 1). The tip of the cannula is then positioned between the anterior and posterior fascia of the rectus abdominis muscle. Electrical impedance is checked confirming a normal, closed electrical circuit. Subsequently, the sensation testing mode (50 Hz, 0.3–0.5 V) is started. As the nerve is often not visible using US, this step is crucial for nerve localization. Sensations such as paresthesia, numbness or prickly sensations should occur at less than 0.5 V if the needle’s position is correct [16]. The cannula is subsequently connected to the PRF Generator (G4, Cosman Medical, MA, USA) using the following settings: 45 V, <42 °C, 20 msec and 2 Hz. Treatment is applied for 6 min.

**Fig. 1 Fig1:**
[figure not shown]
Ultrasound-guided placing of the pulsed radiofrequency (PRF) cannula at the tender point

#### Neurectomy arm

Patients assigned to the neurectomy arm will be operated on in a daycare setting. The area of maximal pain is identified and marked. Once general anesthesia is administered, the anterior sheath of the rectus abdominal muscle is exposed via a ±5-cm transverse skin incision. The neurovascular bundle penetrating into the subcutaneous fat through the pre-existent fascial foramen is identified (Fig. 2). The fascia is widened and the bundle and all its branches within a 5-cm radius are ligated and removed. Accompanying vascular structures are also ligated or coagulated. The sheath as well as the remainder of the wound are closed in layers using absorbable suturing material.

**Fig. 2 Fig2:**
[figure not shown]
Intraoperative view of a neurovascular bundle (loop) and a nearby branch (loop) perforating the fascial foramina of the anterior sheath of the abdominal rectus muscle

#### Medication

“Escape” medication as currently used for pain reduction is allowed to be continued during the entire study period. In daily clinical practice, patients who underwent a neurectomy are always allowed to take analgesics in the postoperative period. Both groups are allowed to take medications according to their own need whereas quantities are tabulated.

### Outcomes

The primary objective is to compare the effect of PRF with a neurectomy in terms of pain relief at the 8-week follow-up. The outcome is measured using the Numeric Pain Rating Scale (NPRS, 0 = no pain and 10 = excruciating). Pain is measured at t_0,_ before intervention and 8 weeks after allowing the determination of short-term efficacy (t_1_) as shown in the schedule of enrollment, interventions and assessments, according to the SPIRIT Statement (Fig. 3). Long-term efficacy is measured at 6-month follow-up (t_2_). Success is defined as more than 50% NPRS pain reduction following intervention.

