### Sample size

Sample size estimation is based on a “responder” analysis, as recommended by the Initiative on Methods, Measurement and Pain Assessment in Clinical Trials (IMMPACT) Group recommendations [21]. Effect sizes were estimated on the basis of published academic literature. Neurectomy is considered successful in 70% [13, 22–25]. Regarding the potential efficacy of PRF treatment, a mean effect size was estimated at 30%. There is no available academic literature apart from two case reports on the use of PRF in ACNES patients. The targeted effect size is a difference in proportion responding to treatment (neurectomy versus PRF) of 40%; i.e., 70% responding in neurectomy the group versus 30% in the PRF group. Using G*Power 3.1.7 software, 80% power and a two-tailed alpha of 5%, 58 participants are needed to demonstrate a potential effect of either type of treatment on pain relief. With an allowance for attrition of 10% in both arms at 6-month follow-up, we will aim to recruit a total of 66 patients.

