### Statistical methods

All analyses are performed using the Statistical Package for the Social Sciences (SPSS) version 21 for Windows. Categorical variables are described as frequencies. Continuous data are tested for normality and are presented as means with standard deviation (±SD) or median values (range) as appropriate. The primary outcome measure is pain relief using the NPRS as compared to the preintervention pain levels (t_0_). Data of the PRF and neurectomy groups will be compared using the Student’s *t* test or the Wilcoxon signed-rank test, as appropriate. Secondary outcomes will be compared between groups at various time points (baseline, 8-week follow-up and 6-month follow-up). They will be compared to preintervention values using Student’s *t* test or the Wilcoxon signed-rank test as appropriate. A *p* value < 0.05 is considered significant. Analysis of data will be done as randomized (the intention-to-treat analysis) and secondary “as-treated.”

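### At 6 months the as-randomised "Long-term efficacy is measured at 6-month follow-up" comparison sets PRF followed by neurectomy on failure against immediate neurectomy, so it cannot be read as the long-term efficacy of PRF

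*Protocol article*

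**What the plan says.** The design is randomised 1:1 "with a one-way optional crossover at 8 weeks" (Trial design). The abstract gives the rule: "At the 8-week follow-up visit, unsuccessful PRF patients are allowed to cross over to a neurectomy". It also says "The study is terminated 6 months after receiving the final procedure".

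Under Outcomes, "The primary objective is to compare the effect of PRF with a neurectomy in terms of pain relief at the 8-week follow-up" (t1). The same paragraph adds "Long-term efficacy is measured at 6-month follow-up" (t2) and defines success as an NPRS reduction of more than 50% following intervention. It does not say whether that means the assigned, the first or the last intervention.

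Under Statistical methods, "Analysis of data will be done as randomized (the intention-to-treat analysis", and the sentence goes on to add a secondary as-treated analysis. Secondary outcomes are compared between groups at baseline, 8 weeks and 6 months. No separate rule is given for 6 months.

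Under Sample size, the planning rates are 70% responders with neurectomy and 30% with PRF. The recruitment target is set "With an allowance for attrition of 10% in both arms at 6-month follow-up".

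**The concern.** Crossover runs one way only, from PRF to neurectomy, and only for patients in whom PRF has failed. If a PRF-arm patient has surgery after week 8 and is then assessed at t2 as randomised, any relief from the surgery is credited to the PRF arm. The result is a sound comparison of two treatment strategies, but the article names it efficacy and nowhere calls it a strategy comparison.

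The Discussion asks whether PRF is an effective option that would reduce the need for surgery. A small 6-month difference could be taken to mean that PRF holds up as well as neurectomy, when it may arise because many PRF patients had had the neurectomy. The 6-month between-group comparisons of quality of life, disability, neuropathic characteristics, medication and satisfaction are affected in the same way.

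**Working it through.** **The plan's own figure.** For 70% v 30%, two-sided 5% and 80% power, the uncorrected two-proportion formula gives 23.3, so 24 per arm (48 in total). With the continuity correction it gives 29 per arm, or 58, as stated. Exact Fisher power at 29 per arm is 81.4%. Allowing for 10% attrition, 29/0.9 = 32.2, so 33 per arm and 66 in total, as stated. Crossover starts at the t1 visit, so none of this changes.

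**Inputs for 6 months.** From the document: neurectomy success 0.70; PRF success at 8 weeks 0.30, so 0.70 of the PRF arm may qualify for crossover (0.70 × 33 ≈ 23 patients). Not in the document, and therefore assumed:
- c, the share of PRF failures who cross over
- q, neurectomy success in those patients
- s, the share of 8-week PRF responders still responding at 6 months

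Failures who do not cross over are taken to remain failures, and neurectomy success is taken to be 0.70 at 6 months as well.

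**Formula.** PRF-arm success as randomised = 0.30s + 0.70cq. Difference (neurectomy minus PRF arm) = 0.70 − 0.30s − 0.70cq. Without crossover it would be 0.70 − 0.30s. Crossover therefore removes 0.70cq from the contrast, whatever the durability of PRF.

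**With q = 0.70 and s = 1:**

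| Uptake c | PRF arm | Difference |
|---|---|---|
| 0% | 30.0% | +40.0 points |
| 50% | 0.30 + 0.70 × 0.5 × 0.7 = 54.5% | +15.5 |
| 80% | 0.30 + 0.70 × 0.8 × 0.7 = 69.2% | +0.8 |
| 100% | 0.30 + 0.70 × 1 × 0.7 = 79.0% | −9.0 |

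The difference is zero at c = 0.40/0.49 = 81.6%. Fisher power for the responder comparison at 29 per arm falls from 81.4% to 14.9% at 50% uptake and 2.5% at 80%. The last figure only says that almost no difference is left to detect.

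**Sensitivity at full uptake (c = 1):**

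| s | q | Without crossover | With crossover |
|---|---|---|---|
| 1 | 0.60 | +40 | −2.0 |
| 1 | 0.50 | +40 | +5.0 |
| 0.8 | 0.70 | +46 | −3.0 |
| 0.67 | 0.70 | +49.9 | +0.9 |
| 0.5 | 0.50 | +55 | +20.0 |

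Reversal needs high uptake, durable PRF response and near-normal surgical success together. Large dilution does not: the least affected row still loses 0.70 × 1 × 0.50 = 35 points.

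**As-treated analysis.** Suppose crossovers are moved to the neurectomy group, with s = 1 and q = 0.70. PRF-group success is then 0.30/(0.30 + 0.70(1 − c)), because only failures leave. This gives 0.30/0.65 = 46% at 50% uptake, 0.30/0.475 = 63% at 75%, and 100% at full uptake, where about 9 of 29 patients remain (29 × 0.30 = 8.7). The neurectomy group stays at 70%. The bias again favours PRF, through selection of responders.

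**The case against.** The strongest reply is that the primary objective is at 8 weeks, before any crossover, so any report would carry an uncontaminated headline result. That stands, and it limits the weight of the point. A reader might infer that the trial's main conclusion or its sample size is compromised; the documents do not support that.

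A second reply is that as-randomised analysis after permitted rescue is valid and fits the aim of sparing patients surgery. That also stands, for a comparison of strategies. The trouble is only the efficacy label.

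A third is that the plan adds an as-treated analysis. It does, but the calculation shows that this does not recover the contrast.

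A fourth is that the article never says in terms that relief after surgery is scored as PRF success, and that detail may sit in a fuller document. It is true that the success definition is silent on crossovers. But the article itself fixes the analysis set, the time point and the label, and taken as written these credit the surgery to the PRF arm.

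A fifth is that the magnitudes depend on uptake, success after crossover and durability, none of which is given, and that the planned tests are on NPRS scores rather than a Fisher test on responders. Both are fair. The percentages are scenarios, and the power figures apply to the responder comparison on which the sample size rests.

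A reader might also infer that t2 falls about 8 weeks later, counted from PRF, in crossovers than in other patients. The abstract's sentence on the final procedure defines only when the study ends, and the visit schedule is in Fig. 3, which is not shown. What can be said is that the text available does not settle whether t2 runs from the first or the final procedure.

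**Conclusion.** The point holds for the 6-month comparison only. As written, that comparison contrasts PRF with neurectomy on failure against immediate neurectomy, under the name of long-term efficacy. With the planning rates, 70% success after crossover and lasting PRF response, the 40-point difference shrinks to 15.5 points at 50% uptake and 0.8 at 80%, and reverses by 9 at full uptake. With durability and post-crossover success both at 50% and full uptake, it is 20 points rather than 55. The size of the dilution, 0.70cq, depends on uptake and surgical success and would be modest if few patients cross over: 12 points at 25% uptake with q = 0.70. Cancellation or reversal is possible but not inevitable. Neither planned analysis estimates 6-month PRF efficacy without this distortion. Severity: should be fixed; secondary time point.

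**What to change.** 1. For 6-month PRF efficacy, analyse responders as randomised, with the existing definition of more than 50% reduction, and count any PRF-arm neurectomy before t2 as PRF non-response. With s = 1 this keeps PRF at 30% against 70%.
2. Report the plain as-randomised 6-month results, for pain and all secondary outcomes, as a comparison of two strategies. The non-response rule covers only the responder endpoint, so for the questionnaire outcomes the correct label is the remedy.
3. Do not present the as-treated result as evidence of PRF efficacy.
4. State that t2 runs from the first assigned procedure in both arms, and report crossovers' post-neurectomy visits separately. If Fig. 3 already fixes this, say so in the text.

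The crossover rule and the sample size stay as they are, and no extra patients are needed. The cost is analysis wording and a clear definition of t2, best settled before the 6-month data are analysed. The 6-month PRF rate will look less favourable. Because the non-response rule can apply only in the PRF arm of an unblinded trial, the strategy result should be shown beside it.

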**Fig. 3 Fig3:**
[figure not shown]
Content for the schedule of enrollment, interventions and assessments, according to the Standard Protocol Items: Recommendations for Interventional Trials (SPIRIT) Statement [12]

Secondary outcomes include the effect of PRF or neurectomy on quality of life, disability, neuropathic characteristics, medication usage and satisfaction. The Short Form Health Survey-12 questionnaire (SF-12) is used for measuring quality of life and interference from pain [17]. Patient disability will be measured with the Pain Disability Index (PDI) and the Brief Pain Inventory (BPI) [18, 19]. The Douleur Neuropathique (DN4) is used in order to discriminate between neuropathic and non-neuropathic pain [20]. Medication usage prior to, and after, treatment will be recorded using World Health Organization (WHO) pain steps. Patient satisfaction is recorded using the Patient Global Impression of Change (PGIC, 1 very much worse to 7 very much improved) and Verbal Rating Scales methodology (VRS, 1 = “I am very satisfied” and 5 = “Pain is worse after treatment”) [4, 21].

All adverse events (AEs) reported spontaneously by the patient, or observed by the investigators or their staff, will be recorded.

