### Blinding

Blinding of patients, surgeons and pain specialists is not possible due to the characteristics of both treatments (minimally invasive treatment without general anesthesia versus invasive treatment with the use of general anesthesia).

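### The only adverse-event collection the article describes is passive, which fits poorly with its aim of detecting PRF side effects and risks under-counting and unequal capture between arms

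*Protocol article*

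**What the plan says.** All places are in the protocol article.

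- **Methods, Outcomes** (last sentence): "All adverse events (AEs) reported spontaneously by the patient, or observed by the investigators or their staff, will be recorded".
- **Methods, Trial design**, on the purpose of the study: "it is designed to attain more knowledge on the use of PRF on peripheral nerves and to detect possible side effects".
- **Abstract, Methods**, which ends its list of secondary outcomes with "use of analgesics and unanticipated adverse events".
- **Methods, Outcomes**, whose own list leaves adverse events out: "Secondary outcomes include the effect of PRF or neurectomy on quality of life, disability, neuropathic characteristics, medication usage and satisfaction".
- **Methods, Blinding**: "Blinding of patients, surgeons and pain specialists is not possible due to the characteristics of both treatments".
- **Abstract, Methods**, on crossover: "At the 8-week follow-up visit, unsuccessful PRF patients are allowed to cross over to a neurectomy".

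The Statistical methods section gives baseline, 8 weeks and 6 months as the time points for comparing secondary outcomes between groups. The schedule of assessments (Fig. 3) is not reproduced in the text available.

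**The concern.** An event that the patient volunteers, or that staff notice, depends on someone thinking it worth mentioning or being placed to see it. That is a weak instrument for a stated aim of finding side effects, and the aim matters here. The Background says that evidence on PRF in ACNES is limited to two case reports, both of treatment at the dorsal root ganglion, whereas this trial treats the abdominal wall. The efficacy, disability, medication and satisfaction outcomes each have a named scale or classification. Side effects have none.

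Capture could also differ by arm. PRF is a cannula procedure in a pain department. Neurectomy is day surgery under general anesthesia with an incision of about 5 cm. Patients and treating staff know the allocation, so what is noticed and what is mentioned may differ for reasons other than true risk. A low recorded PRF count could then reflect few events or little reporting, and a between-arm difference in counts would mix risk with intensity of observation.

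A smaller point is that the abstract counts unanticipated events, while Methods records all events. Those are different outcomes: an expected postoperative effect falls under one and arguably not under the other.

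**Working it through.** **1. The plan's own figure.** The article's only computed design figure is the sample size, and it supplies the arm size used below. Inputs from the Sample size section are 70% versus 30% response, two-sided 5% alpha and 80% power. The article does not state the test setting used.

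- Uncorrected: n = [1.96·√(2·0.5·0.5) + 0.842·√(0.7·0.3 + 0.3·0.7)]² / 0.4² = 23.3, so 24 per arm (48 in total).
- With continuity correction: n' = (23.3/4)·[1 + √(1 + 4/(23.3·0.4))]² = 28.1, so 29 per arm, or 58. This matches the article.
- Attrition: 29/0.9 = 32.2, so 33 per arm, or 66. This also matches.

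The point does not dispute these numbers. They fix 33 PRF patients.

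**2. Chance of recording no case at all.** The documents give neither an event rate p nor a capture probability c, so both are assumed. With 33 patients, P(no case recorded) = (1 − p·c)³³.

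| True incidence p | c = 1 | c = 0.75 | c = 0.5 | c = 0.3 | c = 0.25 |
|---|---|---|---|---|---|
| 5% | 0.184 | 0.283 | 0.434 | 0.607 | 0.660 |
| 10% | 0.031 | 0.076 | 0.184 | 0.366 | 0.434 |

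The c = 1 column is the part due to sample size alone. At 5% incidence, 18 of the 43 percentage points at half capture would remain under perfect collection. The other 25 (0.434 − 0.184 = 0.250) are due to collection.

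**3. Unequal capture with no true difference.** Capture is assumed to be 90% for neurectomy and 50% for PRF. This direction is chosen for illustration only.

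- True incidence 20% in both arms: expected recorded counts are 33·0.20·0.9 = 5.9 and 33·0.20·0.5 = 3.3.
- True incidence 30% in both arms: recorded rates are 0.30·0.9 = 27% and 0.30·0.5 = 15%, a spurious gap of 12 points. Exact enumeration of the uncorrected chi-square test with 33 per arm rejects at 5% with probability 0.227, against about 0.053 when both arms have the same recorded rate. Nearly all of the rejections (0.226) show the less closely observed arm as safer.

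**4. Timing.** Crossover is possible from week 8 and runs one way, from PRF to neurectomy. Up to week 8 the randomised arms coincide with the procedures. At 6 months the PRF arm may contain patients who have also had surgery, so a count by randomised arm would place surgical events under PRF. Any remedy has to allow for this.

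**The case against.** The strongest reply is that the sentence says which events are recorded. It does not say that patients are never asked. Fig. 3 and the full protocol are not shown, and a standard question or form is the kind of detail an article may leave to them. A reader might infer that spontaneous report and accidental sightings are the sole routes. The text does not go that far: observation by staff can include the scheduled 8-week visit, and nothing in it excludes questioning. What stands against the reply is that the article is not silent. It states a method, and the word it chooses for patient reports means unprompted.

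A reader might also infer that events are in fact under-counted, or that PRF will be made to look safer. No documented rate supports either statement. Both are risks, and the figures above are correct arithmetic on assumed inputs. Even under the assumed 90% and 50% capture, the spurious gap is non-significant about 77% of the time.

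Some harm is already elicited alike in both arms. PGIC and VRS include categories for worsening, PDI and BPI measure disability, and DN4 measures neuropathic features. This narrows the gap. It does not cover wound, anesthetic or other procedural events.

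PRF is also the less invasive option by the nature of the procedures, not by event counts, and the article states no between-arm hypothesis on adverse events. Both points are correct, and they limit the consequence. Finally, the abstract's narrower wording loses no data, because the Methods text is the broader one. That mismatch is editorial.

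**Conclusion.** The point holds in a limited form. The only collection route described is passive, and that is a poor match for a trial that names side-effect detection as an aim. In an unblinded comparison of a needle procedure with surgery it carries a risk of under-counting and of unequal capture. The documents do not allow the size or direction of that risk to be derived. The illustrations rest on assumed incidences (5% to 30%), assumed capture probabilities and 33 patients per arm. They show only that incomplete or unequal capture could matter at this sample size. If the full protocol or the Fig. 3 schedule already contains a standard question, the article need only say so. No figure in the plan is wrong. This is a cheap improvement of minor severity.

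**What to change.** In Methods, Outcomes:

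1. Add one open adverse-event question and a short fixed checklist, identical for every patient in both arms, at the existing 8-week and 6-month contacts. Keep recording spontaneous and observed events.
2. Record the date of each event and the procedure that preceded it.
3. Base the between-arm safety comparison on elicited events up to week 8, before any crossover. Report later events by procedure received.
4. Use one outcome definition throughout, by bringing the abstract's wording into line with the all-events wording in Methods.

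The cost is one extra form page at contacts that already exist, and more minor events recorded in both arms. No extra visit is needed. A checklist makes the asking equal but does not remove reporting that is influenced by knowing the treatment, and the report should say so.
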